### **13.0 CRITERIA FOR REMOVAL FROM STUDY**

Patients will be removed from the study if they experience unacceptable adverse events from acupuncture. If at any time the primary oncologist believes it is in the best interest of the participant to be withdrawn from the study, the participant will be withdrawn. Study subjects also may elect to withdraw from the study. Patients who withdraw will be asked for their reasons defined as: acupuncture treatment inconvenience; belief that treatment is ineffective; data collection inconvenience; medical reasons; or other. Patients who discontinue participation in the study will be asked if they are willing to provide follow-up data or whether they wish to withdraw completely.

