| Study Allocation Belief                                                                                          |   |   |   | X |
| Pain Medication List                                                                                          | X | X | X | X |
| Safety Assessment                                                                                                | X | X | X |   |
| Quantitative Sensory Testing (QST)                                                                               | X |   | X | X |
| Controlled Pain Modulation (CPM)                                                                                 | X |   | X | X |

1. In the case of any missed sessions during the study, the testing, questionnaires and other assessments should occur in the same week as planned. In the case of early discontinuation of treatment, all attempts will be made to collect the questionnaires until the end of the study.
2. ECOG Performance Status will be assessed  $\leq 28$  days before the consent.
3. The medication lists will include both prescription and non-prescription pain medication.
4. Patients will be monitored for side effects at each acupuncture and sham acupuncture session .
5. This will be performed by an IMS research study assistant who will go through training before the initiation of the study. A window of + 1 week applies to the baseline assessments, and a window of +/- 3 days applies to week 8 and week 12 assessments.
6. Can be performed over the phone.

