### **Quantitative Sensory Testing (QST)**

At weeks 0 (Baseline), 8 and 12, all participants will receive QST from a trained research study assistant (RSA). To minimize inter-observer variability in measurement, the same RSA will conduct all pre- and post-measurements for participants when possible. This RSA will be blinded to treatment allocation. Participants will be asked not to take any pain, stimulant, or sedative medication for at least 12 hours prior to the testing session. We will conduct QST in a quiet room with little environmental stimuli to detect tactile threshold (TT), vibration threshold (VT), and thermal threshold (THT). The TT and pressure pain threshold will be evaluated by means of Von Frey’s filaments (Somedic; Stockholm, Sweden), a set of 17 filaments with hairs of different diameters. We will ask the subject to sit in a comfortable position and close their eyes so that the examination is not influenced by visual input. TT will be assessed at the dorsum of the distal interphalangeal joint of the right- and left- middle fingers and both the left and right big toes, as described previously. The VTs will be assessed using a handheld biothesiometer (Bio-Medical Instrument Company; Newbury, Ohio), whose amplitude may be gradually increased until the threshold of vibratory sensation is reached. The VTs will be evaluated at the dorsum of the distal interphalangeal joints of the right

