## **12.0 CRITERIA FOR THERAPEUTIC RESPONSE/OUTCOME ASSESSMENT**

The primary endpoint will be measured by NRS of the most bothersome CIPN symptom and measured at time of consent (baseline) and at 8 weeks, after the final acupuncture session for the acupuncture or sham acupuncture arms and at baseline and after 8 weeks of usual care for patients randomized to the usual care arm. Secondary endpoints will be measured by the FACT/GOG-NTx, NPS, NCI-CTC 4.0, ISI, HADS, BFI, TES, QST, and CPM. Additionally, NRS will be assessed as a secondary aim at baseline, 4 weeks, and 12 weeks for all arms. All non-NRS secondary endpoints will be assessed at baseline, 8 weeks and 12 weeks. The NPS and FACT-GOG/NTX will also be assessed at 4 weeks.

All patients enrolled in the study who completed acupuncture or sham acupuncture will be included in the analyses, and any patients who withdraws from the study or who is lost to followup will be described.

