neuropathy we will use linear regression to assess the association between NRS and TT, VT, and THT at baseline, and the association between change in NRS with change in TT, VT, and THT. For the mechanistic studies, we will use an interaction term between baseline CPM and real acupuncture to predict NRS at 8 weeks:  $NRS_8 = \beta_1 NRS_0 + \beta_2 CPM_0 + \beta_3 \text{Real Acupuncture} + \beta_4 CPM_0 \times \text{Real Acupuncture} + c$ . We will also test acupuncture-induced changes in CPM as  $CPM_8 = \beta_1 CPM_0 + \beta_2 \text{Real Acupuncture} + \beta_3 \text{Any Acupuncture} + c$ . We will also explore the relationship between treatment expectancy and response adjusting for baseline CIPN and treatment arm using multivariable linear regression comparing acupuncture versus sham acupuncture:  $NRS_8 = \beta_1 NRS_0 + \beta_2 \text{Real Acupuncture} + \beta_3 \text{Treatment Expectancy} + c$ . We will also estimate the change in mean HADS, BFI and ISI scores from baseline to 8 and 12 weeks along with a 95% confidence intervals, separately. We will also estimate the proportion of patients with a dose reduction and the proportion of patients who experience a dose escalation of neuropathy medication during the course of the 12 weeks along with an upper 90% confidence interval. All analyses will be by intent to treat, with participants analyzed according to allocation irrespective of treatment actually received. We will use multiple imputation, including 4 week outcome, for missing data at 8 weeks. Patients with 4 and 8 week outcomes are missing, they will not be included in the analysis.

For a trial with 25 patients per group, and an anticipated correlation between baseline and follow-up measures of 0.5, we will be able to calculate the upper bound of a one-sided, 90% confidence interval for the coefficients of any treatment and real acupuncture to approximately 0.35 standard deviations.

Last year, 935 solid tumor survivors had a diagnosis of persistent CIPN 3 months after chemotherapy completion. A recent study showed that among breast cancer survivors 28% reported moderate to severe CIPN 3 months after chemotherapy completion. Therefore, we anticipate 262 patients are eligible per year for our proposed study. Assuming at least a 15% enrollment rate of the eligible patients the estimated accrual is 3-4 patients per month, the estimated accrual period is between 19 and 25 months in order to identify 75 eligible patients.

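### Section 13 takes patients with unacceptable acupuncture adverse events out of the study, while Table 2 footnote 1 keeps treatment stoppers in follow-up; the two must be reconciled to protect the intent-to-treat analysis

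*Protocol*

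**What the plan says.** Four places in the protocol bear on what happens to a patient who stops treatment.

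- **Section 13.0** on adverse events: "Patients will be removed from the study if they experience unacceptable adverse events from acupuncture". The same paragraph lets the primary oncologist withdraw a participant and lets patients withdraw themselves. It ends: "Patients who discontinue participation in the study will be asked if they are willing to provide follow-up data or whether they wish to withdraw completely".
- **Table 2, footnote 1** (Section 1.0): "In the case of early discontinuation of treatment, all attempts will be made to collect the questionnaires until the end of the study". The sentence before it, on missed sessions, keeps testing, questionnaires and other assessments in their planned week. The sentence on early discontinuation names questionnaires only.
- **Section 12.0**: "All patients enrolled in the study who completed acupuncture or sham acupuncture will be included in the analyses". Withdrawals and losses to follow-up are to be described.
- **Section 14.0**: "All analyses will be by intent to treat, with participants analyzed according to allocation irrespective of treatment actually received". For missing values: "We will use multiple imputation, including 4 week outcome, for missing data at 8 weeks". Patients with neither a week 4 nor a week 8 outcome are left out.

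Section 8.0 schedules QST and CPM for everyone at baseline, week 8 and week 12. Table 2 shows no week 4 measurement of either.

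**The concern.** An intent-to-treat analysis needs outcomes from patients who stop their sessions. Footnote 1 is written for that purpose. The adverse-event sentence in Section 13.0 works against it, because it makes an adverse event a reason to leave the study and not only the sessions. Staff handling a patient who stops in week 3 because of an adverse event cannot tell which text governs.

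Two features give this statistical weight. The trigger depends on the arm: it requires an adverse event from acupuncture, and usual care patients are offered acupuncture only after their week 12 assessments. Section 14.0 also has no remedy for a patient who leaves before week 4 and gives no later data, since that patient is excluded. The pilot exists to supply effect, SD and correlation estimates for a definitive trial, so loss that is linked to arm and to tolerability would carry into that design.

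**Working it through.** **1. The texts side by side, for a patient who stops in week 3 after an adverse event**

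| Text | Status of the patient | Data sought |
|---|---|---|
| Section 13.0, adverse-event sentence | Out of the study | Not stated |
| Section 13.0, last sentence | Discontinued participation | Patient is asked; scope for removed patients unclear |
| Table 2, footnote 1 | Off treatment, still followed | Questionnaires; QST and CPM not mentioned |
| Section 12.0 | Not a completer | Described; inclusion in the analyses not provided for |
| Section 14.0 | Analysed as allocated | Imputed if week 8 is missing; excluded if weeks 4 and 8 are both missing |

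The adverse-event sentence and footnote 1 conflict. The last sentence of Section 13.0 and footnote 1 do not, because collecting data always needs the patient's agreement. Section 12.0 conflicts with Section 14.0 on who is analysed.

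**2. Which outcomes could be lost**

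The NRS has a week 4 value, so a patient lost between weeks 4 and 8 can be imputed, and one lost before week 4 is excluded. QST and CPM have no week 4 value, so a missing week 8 test has no interim measurement of its own to support imputation.

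**3. The plan's precision figure, as a yardstick**

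Section 14.0 states about 0.35 SD for a one-sided 90% bound, with 25 per arm and a baseline correlation of 0.5.

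- With baseline adjustment: 1.2816 × √[(1 − 0.5²) × (1/25 + 1/25)] = 0.314 SD.
- Without adjustment: 1.2816 × √(1/25 + 1/25) = 0.362 SD.

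Neither gives exactly 0.35. That difference is a separate matter and nothing here rests on it. The yardstick is roughly 0.31 to 0.35 SD.

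**4. Effect of selective loss**

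If k of 25 acupuncture patients are lost and would have scored d SD worse than those retained, the mean of the retained patients is too favourable by (k/25) × d. The protocol states neither k nor d. The range d = 0.5 to 1.5 SD is an assumption.

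| k lost | Shift in mean | Acupuncture v sham half-width |
|---|---|---|
| 1 | 0.02 to 0.06 SD | 0.317 SD |
| 3 | 0.06 to 0.18 SD | 0.324 SD |
| 5 | 0.10 to 0.30 SD | 0.333 SD |

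These are complete-case figures. Imputation would reduce them for patients with a week 4 value.

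**5. How many removals are plausible**

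Section 11.0 lists the most common acupuncture side effects at under 5% and less common ones at under 1%. Reading those ceilings as per-patient removal rates is an assumption, and a high one, since most listed events are minor.

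- At 5%: 25 × 0.05 = 1.25 expected; P(at least one) = 1 − 0.95²⁵ = 72%; P(three or more) = 13%.
- At 1%: 25 × 0.01 = 0.25 expected; P(at least one) = 1 − 0.99²⁵ = 22%.

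**The case against.** The best defence is that the protocol already provides for these patients. Section 13.0 itself asks for follow-up data, and Table 2 footnote 6 allows the NRS, the other questionnaires, the NCI-CTC grade and the medication list to be done by phone. A stopper can therefore still give the primary endpoint. The protocol's own safety information (Sections 3.0, 11.0 and 17.0) points to few removals. Seeking only questionnaires after discontinuation can also be defended for mechanistic tests, because QST and CPM mean 12 hours without pain medication, painful heat and a cold-water immersion.

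Most of this stands, and it rules out several stronger readings that a reader might infer.

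- **Three incompatible rules.** There is one direct conflict on follow-up plus an unclear scope for QST and CPM. The Section 8.0 testing schedule is general and is not a rule for stoppers.
- **Outcomes will be lost.** Loss is a risk and is not prescribed.
- **Loss from both needled arms, with usual care followed in full.** Sham is a non-insertion procedure, so the trigger falls mainly on real acupuncture. The oncologist and patient-choice routes apply to every arm, and Section 4.2 offers later acupuncture partly to keep controls in the study. The net direction of differential loss is unknown.
- **A sizeable bias.** Taking the 12% duloxetine dropout quoted in Section 3.0 and a 2-point deficit gives 3/25 × 2 = 0.24 NRS points. The 12% is overall dropout on an oral drug, and the 2 points have no source in the protocol as a difference between removed and retained patients.

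The defence does not settle which text governs a patient removed by the investigator or oncologist. Asking such a patient whether they will give data is also a weaker default than footnote 1.

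**Conclusion.** The point holds as a conflict of wording with a small expected effect. Section 13.0 and Table 2 footnote 1 disagree on whether an adverse event ends study participation. The reach of Section 13.0's request for follow-up data is unclear, and so is the collection of QST and CPM after stopping. Because the adverse-event trigger cannot apply to usual care before week 12, and Section 14.0 excludes patients missing weeks 4 and 8, outcome loss could depend on arm.

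Under the assumed deficit of 0.5 to 1.5 SD, one lost patient shifts the acupuncture mean by 0.02 to 0.06 SD, at most about a fifth of the 0.31 to 0.35 SD half-width. It becomes material only at about three to five losses, which the listed side-effect rates make unlikely. The case for acting rests on the contradiction and the low cost of removing it. The most direct clash with intent to treat is the completer sentence in Section 12.0, because a fully followed stopper could still be left out under it.

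**What to change.** Reconcile Table 2 footnote 1 with Sections 12.0, 13.0 and 14.0:

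1. Define stopping study sessions and withdrawing from data collection as separate events, and record them separately.
2. State that patients who stop sessions for any reason, in any arm, stay in scheduled outcome follow-up by default unless they decline. This should cover at least the NRS and the other assessments that Table 2 allows by phone.
3. Say whether the closing request for follow-up data in Section 13.0 covers patients removed for an adverse event or withdrawn by the oncologist.
4. State whether clinic QST and CPM are also sought from patients who have stopped, and name the added burden. Either choice is workable if it is explicit.
5. Bring the Section 12.0 completer sentence into line with the intent-to-treat statement in Section 14.0.

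When sessions should stop, and the oncologist's authority to withdraw a patient, are clinical matters that this change leaves alone.

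The cost is a wording amendment plus some phone contact for assessments already scheduled. If QST and CPM are included, patients who have stopped would be asked to attend up to two clinic visits (weeks 8 and 12) with the medication pause and painful stimuli these tests involve, and they may decline.

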### **14.0 BIOSTATISTICS**

The main objective of this study is to provide preliminary data on the effect of acupuncture in reducing persistent CIPN symptoms from baseline to after 8 weeks of acupuncture or sham acupuncture as compared to a usual care control in order to design a fully powered randomized trial of acupuncture versus sham acupuncture. The enrollment goal is 75 patients.

To help plan the definitive trial, we will derive estimates for the standard deviation of all endpoints and the correlation between baseline and follow-up for each endpoint. For each of the patient reported outcomes (NPS, FACT/GOG-NTx, NRS) analysis will be by ANCOVA with the baseline score and most bothersome CIPN symptom as covariates.. Treatment will be coded as dummy variables for any treatment and real acupuncture, hence the three groups will be coded 1/1, 0/1, and 0/0 for acupuncture, Sham acupuncture, and UC respectively. Similarly, to account for type of most bothersome CIPN symptom (tingling vs numbness vs pain) dummy variables for tingling, numbness, and pain will be coded 1/0, 0/1, and 0/0, respectively. Where the week of follow-up is given in the subscript, we will calculate:  $NRS_8 = \beta_1 NRS_0 + \beta_2 \text{Real Acupuncture} + \beta_3 \text{Any Acupuncture} + \beta_4 \text{Tingling} + \beta_5 \text{Numbness} + c$ . The primary endpoint will be NRS of the most bothersome CIPN symptom at 8 weeks.

We will estimate the change in the proportion of patients with a CIPN severity of grade 3 or higher according to the NCI-CTC 4.0 from baseline to 8 and 12 weeks along with an exact 95% confidence interval, separately. To explore the relationship between quantitative sensory testing (QST) and

neuropathy we will use linear regression to assess the association between NRS and TT, VT, and THT at baseline, and the association between change in NRS with change in TT, VT, and THT. For the mechanistic studies, we will use an interaction term between baseline CPM and real acupuncture to predict NRS at 8 weeks:  $NRS_8 = \beta_1 NRS_0 + \beta_2 CPM_0 + \beta_3 \text{Real Acupuncture} + \beta_4 CPM_0 \times \text{Real Acupuncture} + c$ . We will also test acupuncture-induced changes in CPM as  $CPM_8 = \beta_1 CPM_0 + \beta_2 \text{Real Acupuncture} + \beta_3 \text{Any Acupuncture} + c$ . We will also explore the relationship between treatment expectancy and response adjusting for baseline CIPN and treatment arm using multivariable linear regression comparing acupuncture versus sham acupuncture:  $NRS_8 = \beta_1 NRS_0 + \beta_2 \text{Real Acupuncture} + \beta_3 \text{Treatment Expectancy} + c$ . We will also estimate the change in mean HADS, BFI and ISI scores from baseline to 8 and 12 weeks along with a 95% confidence intervals, separately. We will also estimate the proportion of patients with a dose reduction and the proportion of patients who experience a dose escalation of neuropathy medication during the course of the 12 weeks along with an upper 90% confidence interval. All analyses will be by intent to treat, with participants analyzed according to allocation irrespective of treatment actually received. We will use multiple imputation, including 4 week outcome, for missing data at 8 weeks. Patients with 4 and 8 week outcomes are missing, they will not be included in the analysis.

For a trial with 25 patients per group, and an anticipated correlation between baseline and follow-up measures of 0.5, we will be able to calculate the upper bound of a one-sided, 90% confidence interval for the coefficients of any treatment and real acupuncture to approximately 0.35 standard deviations.

Last year, 935 solid tumor survivors had a diagnosis of persistent CIPN 3 months after chemotherapy completion. A recent study showed that among breast cancer survivors 28% reported moderate to severe CIPN 3 months after chemotherapy completion. Therefore, we anticipate 262 patients are eligible per year for our proposed study. Assuming at least a 15% enrollment rate of the eligible patients the estimated accrual is 3-4 patients per month, the estimated accrual period is between 19 and 25 months in order to identify 75 eligible patients.

If the confidence interval for acupuncture treatment effect includes clinically relevant effects, we will then perform a sample size calculation of a future two arm randomized trial using estimates of standard deviation of the CIPN score, the correlation between baseline and followup measures from the current trial. We will calculate the accrual rate along with a 95% Poisson confidence interval (with an exact 95% confidence interval). With a sample size of 75 patients the 95% confidence interval for the accrual rate will be  $\pm 23\%$ . Combining the resulting sample size with the accrual rate will provide an estimate of trial duration, along with an upper and lower bound.

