## **4.0 OVERVIEW OF STUDY DESIGN/INTERVENTION**

### **4.1 Design**

This is a single-center, three-arm, phase IIB, pilot randomized controlled trial comparing acupuncture, sham acupuncture and usual care. We will enroll 75 solid tumor cancer survivors who completed chemotherapy at least 3 months prior who have persistent moderate to severe CIPN symptoms defined as at least one NRS  $\geq 4$  (25 patients in each arm). With a total sample size of 75 this trial will provide preliminary data on the effects of treating patients with acupuncture to reduce persistent CIPN as measured by NRS and other CIPN measurements such as NPS and FACT/GOG-Ntx when compared to sham acupuncture or usual care. The primary end point of this study is NRS of the patients' most bothersome CIPN symptom (tingling, or numbness or pain) at week 8. It is the CIPN symptom having the maximum NRS measured at baseline. If more than one symptom share the maximum value, we would ask the patient to pinpoint the most bothersome symptom and use that one as the primary endpoint. Secondary end points are NPS, FACT/GOG-Ntx, ISI, HADS, BFI, TES, QST and CPM. These data will then be used in the design of a fully powered trial.

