## **15.2 Randomization**

Randomization is implemented via MSKCC's Clinical Research Database (CRDB), a secure system that ensures that treatment allocation cannot be guessed before or modified after a patient is registered on trial, allowing for full allocation concealment. Randomization will be 1:1:1 (ACU:Sham: UC) using randomly permuted blocks of random length stratified by type of the most bothersome CIPN symptom (tingling vs numbness vs pain) and severity of such symptom (moderate 4-6 vs 7-10 on NRS). Once the patient is randomized, the CRS or CRM will inform the acupuncturist of the patient's group assignment and the RSA of whether the patient was assigned to an acupuncture group or to the UC group. The RSA's and patients will be blinded to which acupuncture group the patient was assigned. The acupuncturists will be the only ones unblinded. The rest of the study co-investigators and staff will remain blinded.

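### Randomisation is stratified by NRS severity, but the NPS, FACT/GOG-Ntx and CPM models leave severity out, so their intervals may be slightly too wide

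*Protocol*

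**What the plan says.** Protocol Section 15.2 describes a 1:1:1 allocation "using randomly permuted blocks of random length stratified by type of the most bothersome CIPN symptom" and by "severity of such symptom (moderate 4-6 vs 7-10 on NRS". Three types by two severity levels make six strata. Section 4.2 describes the same two factors.

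Protocol Section 14.0 then fixes the models. For NPS, FACT/GOG-Ntx and NRS, "analysis will be by ANCOVA with the baseline score and most bothersome CIPN symptom as covariates". The equation written out for week-8 NRS has baseline NRS, two treatment indicators and two indicators for symptom type, with no separate severity term. For CPM the sentence opening "We will also test acupuncture-induced changes in CPM as" gives an equation with baseline CPM and the two treatment indicators only.

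Protocol Section 4.1 defines the symptom used for the primary endpoint: "It is the CIPN symptom having the maximum NRS measured at baseline". Nothing in the protocol explains why one stratification factor is kept in the patient-reported outcome models and the other is not, or why both are absent from the CPM model.

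**The concern.** When randomisation balances a prognostic factor across arms and the analysis model omits it, the variation due to that factor stays in the residual. The model-based standard error then ignores the balance that the design achieved and overstates the sampling error of the treatment coefficient.

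For NRS this hardly arises, because baseline NRS of the most bothersome symptom is the variable that the severity stratum splits. For NPS and FACT/GOG-Ntx, the baseline score is naturally read as that instrument's own baseline, which is not the NRS. For CPM the equation is explicit. In those three models neither baseline NRS nor the stratum appears.

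At stake is the width of the reported intervals for secondary and mechanistic treatment effects, in a pilot whose purpose is to report estimates with intervals.

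**Working it through.** **1. The plan's own precision figure.** Section 14.0 takes "For a trial with 25 patients per group, and an anticipated correlation between baseline and follow-up measures of 0.5" and states the "upper bound of a one-sided, 90% confidence interval for the coefficients of any treatment and real acupuncture to approximately 0.35 standard deviations". For one pairwise coefficient under ANCOVA, the distance from estimate to bound is z(0.90) × √(2/25) × √(1 − 0.5²) = 1.2816 × 0.2828 × 0.8660 = 0.314 SD (0.317 with t on 70 df). Without baseline adjustment it is 0.362. Neither gives 0.35, but the stated value is wider than its own inputs imply. This is a separate matter and does not bear on the present point. I use 0.314 as the base.

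**2. Which models lack severity.**

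| Outcome at week 8 | Baseline term | Symptom type | Severity |
|---|---|---|---|
| NRS (primary) | baseline NRS | yes | carried by baseline NRS |
| NPS | own baseline | yes | absent |
| FACT/GOG-Ntx | own baseline | yes | absent |
| CPM | own baseline | absent | absent |

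Under two assumed distributions of baseline NRS over 4 to 10, the 4-6 or 7-10 split correlates 0.84 and 0.87 with baseline NRS itself. The primary model therefore already holds severity, in finer form.

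**3. Effect on interval width.** Let r_p be the partial correlation of the severity stratum with the week-8 outcome, given the other covariates. Adding severity multiplies the half-width by √(1 − r_p²), so leaving it out makes the interval wider by 1/√(1 − r_p²) − 1. The documents do not give r_p; the range 0 to 0.4 is my assumption. The last column is from simulation, 4,000 trials per setting: 75 patients, six strata, own-baseline correlation 0.5, and assumed block lengths of 3 and 6 with 30% or 50% of patients in the severe stratum. It includes the lost degree of freedom.

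| Assumed r_p | Half-width with severity (SD) | Excess width without it | Simulated ratio, without/with |
|---|---|---|---|
| 0 | 0.314 | 0% | 0.998 |
| 0.1 | 0.312 | 0.5% | 1.003-1.004 |
| 0.2 | 0.308 | 2.1% | 1.019 |
| 0.3 | 0.299 | 4.8% | 1.047-1.048 |
| 0.4 | 0.288 | 9.1% | about 1.09 |

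At r_p = 0.3 the excess is 0.314 − 0.299 = 0.015 SD.

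**4. Which values of r_p are plausible.** Write r_b for the correlation of severity with the scale at baseline and r_8 for that at week 8. With own-baseline correlation 0.5, r_p = (r_8 − 0.5 r_b) / √[(1 − r_b²)(0.75)].
- If severity relates to the scale no more strongly at week 8 than at baseline (r_8 = r_b), then r_b = 0.2 gives r_p = 0.1/0.849 = 0.12 and an excess of 0.7%. With r_b = 0.4, r_p = 0.2/0.794 = 0.25 and the excess is 3.3%.
- To reach r_p = 0.4 with r_b = 0.2 needs r_8 = 0.1 + 0.4 × 0.849 = 0.44. With r_b = 0.4 it needs r_8 = 0.2 + 0.4 × 0.794 = 0.52, which is more than the scale's own baseline achieves.

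The 9% is therefore an extreme.

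**5. Validity.** Without severity in the model, simulated coverage of the two-sided 95% interval was 94.8% to 96.6%. The intervals are valid or slightly conservative.

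**6. Reported width against real precision.** At r_p = 0.3 the simulated sampling SD of the real-acupuncture coefficient was 0.2405 without severity and 0.2384 with it (30% severe), and 0.2441 and 0.2428 (50% severe). That is a change of 0.9% and 0.5%. At r_p = 0.4 the change was about 2% (0.2310 to 0.2265; 0.2335 to 0.2286). Stratification has already secured most of the precision, so the added term mainly corrects the reported standard error.

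**The case against.** The strongest case for leaving the plan alone is that nothing is contradicted. The protocol never undertakes to adjust for every stratification factor, the primary model is sound, the affected analyses are secondary or mechanistic, and the error is in the safe direction. For CPM, a difference in heat-pain ratings under cold-water conditioning, nothing in the documents shows that NRS severity is predictive at all. All of this stands and keeps the point small. It does not justify omitting a design factor from models that the protocol itself writes out, when including it is almost free.

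A reader might infer more, and four such readings fail:
- **That the intervals are too wide as a matter of fact.** This needs a non-zero partial correlation, which the documents do not give. At zero there is no excess.
- **That the omission is like losing a fifth of the patients.** Squaring 1.09 gives about 1.19, but that describes reported width at an extreme setting. The true sampling SD changes by about 2% there (1.02² = 1.04), because stratification already balances severity.
- **That planning of the definitive trial is harmed.** Section 14.0 sizes that trial from the endpoint standard deviation and the baseline/follow-up correlation. Neither depends on this covariate.
- **That the primary NRS model or every continuous outcome needs the term.** Baseline NRS already carries severity in the primary model. HADS, BFI and ISI are planned as mean changes with intervals, not through these models.

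**Conclusion.** The point holds as a modest improvement to three secondary models. Severity is a randomisation stratum that the NPS, FACT/GOG-Ntx and CPM models leave out, and the CPM model leaves out symptom type as well. If severity predicts these outcomes beyond their own baselines, the intervals for the treatment coefficients are too wide by about 0-5% for a partial correlation of 0 to 0.3, and about 9% at 0.4. There is no bias and no loss of coverage.

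The size rests on the assumed partial correlation, on the protocol's 0.5 baseline/follow-up correlation, and on reading the baseline score for NPS and FACT/GOG-Ntx as each scale's own. The primary endpoint and the inputs to the next trial's sample size are not affected.

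**What to change.** In Protocol Section 14.0, add baseline NRS of the most bothersome symptom, or the 4-6 or 7-10 stratum indicator, to the NPS, FACT/GOG-Ntx and week-8 CPM models. Add the two symptom-type indicators to the CPM model. Leave the NRS model as written.

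The cost is one residual degree of freedom for NPS and FACT/GOG-Ntx (75 patients less 6 parameters leaves 69, falling to 68) and three for CPM (75 less 4 leaves 71, falling to 68). In simulation, adding the single severity term when it has no prognostic value widened the interval by about 0.2%; the three-term change to the CPM model was not simulated separately. All the variables are already collected at baseline.
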